**Fig. 3 Fig3:**
[figure not shown]
A power contour plot. Power analysis suggests that a paired samples t-test including 38 participants will reliably detect (power = 80%) an effect size of 0.82, or higher. Statistical power is also shown by assuming smaller or larger hypothetical effect sizes. Analysis and visualisation were performed using the ‘jpower’ JAMOVI module: https://github.com/richarddmorey/jpower

#### Recruitment

Participants are recruited via Oslo University Hospital, Ahus Hospital, Oslo-, Bærum- and Drammen municipalities, which are located in south-eastern Norway (Table 2). We will invite back people with communication difficulties who have already participated in previous phases of the project two years ago [47], as well as new participants. The investigators will present the study to the local municipalities’ administrators, who will be encouraged to contact the leaders of the districts’ communal residences for persons with ID. Professional caregivers at the care homes will approach the parents or legal representatives of potential participants with written materials describing the study. All recruitment channels will direct the interested individuals to the investigators, and written consent will be obtained from the parents or legally authorized representatives of the participants.

#### Method of assigning participants to treatment groups

The study design employs an early and a delayed intervention group to distinguish the effects of formal routine changes from increased attentiveness due to study participation and effects of instantaneous changes in care. The early intervention group will start intervention in week three while the delayed group will continue data collection for another two weeks before introducing procedure changes. Patients will be randomly assigned to one of the two groups (Fig. 1) on a 1:1 ratio using a computer-generated randomization scheme.

#### Blinding

The identity of test and delayed intervention treatments will not be known when analysing data on the secondary outcome measure. Access to the randomization code will be strictly controlled.

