## Methods

### Study design overview

This is a single centre, controlled, randomized trial with 38 non-verbal participants, testing if HR-guided interventions in suspected painful settings will change the incidence of pain. The study design includes a two-week *pre-intervention*, consisting of continuous HR registering across four potentially painful settings; and an *intervention phase* consisting of formal change in procedure for the identified painful situation (Fig. 1). The interventions are in one of four forms: changes in 1) physiotherapy techniques, 2) preparations for putting on casts, 3) lifting techniques or 4) personal hygiene procedures. HRV and inflammatory cytokines (MCP-1, IL-1RA, IL-8, TGFβ1, and IL-17) are measured at the beginning, midway, and end of the study period to assess change in long-term pain. Participants will be randomly assigned to either an early intervention group or a delayed intervention group in a 1:1 ratio using a computer-generated randomization scheme. This will differentiate the effect of formal change in routine from increased attentiveness due to study participation, and instant changes made when the HR band signify obvious acute pain (such as skin pinched while putting on a cast). Overview over measures and objectives is given in Table 1.

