### Study design

#### Intervention

The intervention comprises individualized routines to reduce pain in potential pain-inducing settings.

In the pre-intervention phase, HR is continuously collected for 8 h/day across potentially painful care situations. The primary caregiver will report on situations with an HR increase (Figs. 4 and 5).

As the caregiver is not blinded to the HR increases during the registration phase, we expect instantaneous changes made when the HR band communicated obvious acute pain (e.g. skin pinched while putting on cast). These instantaneous, non-formalized changes made by each caregiver is not regarded as “change in routine” but are registered as HR-informed adaptations. The intervention consists of a formal change in routine, and involved changes is written routine and training of staff for the chosen situation. Allocation into an early group and a delayed group helps distinguish the non-formal adaptations based on HR from the effect of formal changes in procedures of care.

Based on the two-week pre-intervention phase, one of four types of care procedures are chosen as the intervention target: 1) physiotherapy, 2) applying cast on spastic limb, 3) transportation/being lifted and 4) personal hygiene procedures. If there are several situations identified as candidates for intervention, selection will be based on a) level of reproducibility and b) magnitude of HR increase. The procedure must be easily recognizable. The situation should at have an HR-spike occurrence for at least 10 episodes during the recording period (i.e. on average 1 occurrence/day), with at least 80% of the situation resulting in HR-increase (reproducibility).

The intervention will be in one of four forms:changes in physiotherapy, e.g., less rigorous movement in the identified painful stretch,preparations for putting on corrective cast to stabilize joint and/or stretch spastic muscles,change in procedures for transportation/lifting, e.g., new technique or adjustments made to equipment, orrevised personal hygiene procedure.

If none of the predefined interventions fit the chosen stressor, a fitting intervention is constructed and will be described separately and in detail when the results of this study are published.

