#### Analysis of secondary objectives

To test evaluate the effect of using HR in improving care procedures and reducing pain, one-tailed paired samples t-tests are used to test for difference in HRV and cytokine biomarkers (MCP-1, IL-1RA, IL-8, TGFβ1, and IL-17) before and after intervention (secondary hypothesis 1). Cohen’s *d* values [94] will also be calculated to determine the size of the effect. To evaluate the effect of HR-informed changes in procedures, differences in biomarker scores across the early and delayed groups will be analysed using Wilcoxon Signed-rank test, which can evaluate whether the difference scores from each group are not equal (i.e., that they are significantly different). Critical P-values for the five cytokine measurers will be corrected for multiple comparisons using a 5% false discovery rate [95].

To test for significant change in rates of understanding the patient throughout study period (secondary hypothesis 2), we will perform one-tailed paired sampled t-tests. Additionally, Spearman’s rank-order correlation (*r*_s_) is used to investigate relationships between HR measures and caregivers report on NCPC and caregivers report on perceived understanding of the patient.

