## Discussion

In this randomized blinded controlled trial, we aim to study HR to improve communication between patient and caregiver. This clinical study of HR-informed intervention represents an important contribution to the research and practice of developmental disabilities and communication difficulties. Studies on patients with limited communicative abilities are lacking (Table 4). Existing studies investigating severely limited communicative abilities are small and mainly descriptive. Larger studies on technologies for patients with communication disability exclude the most severely debilitated patients. Furthermore, considerable heterogeneity of participant level of communication disability makes for less clinically relevant findings. In the present study we strive to correct this.

**Table 4 Tab4:** Methodological advances of current trial relative to past sensor-technology intervention trials among patients with communication difficulties

Limitations in literature^a^	Current study features
Few controlled trials	Randomized controlled design
Small sample sized/insufficient power/case studies	A sample of 38 patients allowing us to detect an 0.80 effect size
Absence of studies using comparator interventions	Controlling for effect of study participation by including a group with delayed intervention
Exclusion of most vulnerable patients	Inclusion of profoundly disabled patients
Lack of standardized measures and biomarkers	HR, HRV and biochemical biomarkers in blood
No adherence data	Routine signing of protocol by secondary participants to measure adherence
Considerable heterogeneity of participants regarding type and level of communication need	Patients with ID ranging from severe to profound and ranging from ambulant to wheelchair user, loss of eyesight and hearing

^a^Based on published reviews [29, 96], and review of studies on PubMed and Google Scholar using the phrases “sensor-technology intervention intellectual disability” and “technology intervention communication difficulties”

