The ethical implications of this study are complex, particularly regarding the patients’ inability to provide informed consent. The mentioned issue of the caregiver as an intermediary is relevant to the ethical considerations taken when designing the study. An apparent way to bypass the intermediary of the caregiver would be to use video recording in addition to HR. However, HR is generally regarded as less intrusive than video recording and considered more ethically just [97]. If video recordings of caregivers were to be conducted, it would be necessary to obtain informed consent from every caregiver involved, as well as any non-participating patients present in the facility. This would introduce additional ethical considerations related to the proper treatment of human subjects in research. We believe HR is informative yet acceptable, a non-invasive technology, possibly of great beneficence to the patients. Another ethical concern here is the aspect of delayed intervention. Obvious painful situations will be detected during the registration phase, and it is not ethical to postpone making changes in these routines for two or four weeks. This ethical aspect makes for more challenging methodology. However, as these instantaneous adaptations are registered, as well as having a delayed intervention group, results will still be valid for evaluation of HR as a communicative aid.

In conclusion, this trial is a randomized blinded controlled clinical trial that test the applicability of HR to reduce incidence of pain in the participant’s everyday life. We will evaluate how HR can be used to identify potentially painful care procedures that should be re-evaluated in terms of the approach taken; test the effect of HR-informed changes in potentially painful care procedures on biomarkers of pain; and assess how six weeks of communication through HR affects the quality of communication between patient and caregiver. Regardless of outcome, the current study will advance the field of wearable physiological sensor-use in patient care.

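### The Discussion calls the trial blinded, but the only masking described hides the arm at analysis and fits one comparison, the early-versus-delayed biomarker contrast

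*Protocol article*

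**What the plan says.** The Discussion opens with "In this randomized blinded controlled trial, we aim to study HR to improve communication between patient and caregiver" and concludes that "this trial is a randomized blinded controlled clinical trial that test the applicability of HR to reduce incidence of pain". The Study design overview does not use the word: "This is a single centre, controlled, randomized trial with 38 non-verbal participants".

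The Blinding section describes a single mask: "The identity of test and delayed intervention treatments will not be known when analysing data on the secondary outcome measure". It adds that access to the randomization code is controlled. The outcome measure is in the singular and is not named.

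On caregivers, the Intervention section says "As the caregiver is not blinded to the HR increases during the registration phase, we expect instantaneous changes". The intervention is a formal change that "involved changes is written routine and training of staff for the chosen situation". It starts in week 3 in the early group and two weeks later in the delayed group. Caregivers also enter the context for each heart-rate rise (Contextual data collection) and answer the understanding questionnaire at the beginning and end (Caregivers' reports of understanding).

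For HRV and the cytokines, Analysis of secondary objectives plans one-tailed paired t-tests "before and after intervention (secondary hypothesis 1"), and also a comparison of the early and delayed groups. Understanding is tested only as change over the study, again by one-tailed paired t-test.

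**The concern.** A reader who is told that a trial is blinded assumes that the people who deliver care, or at least those who rate outcomes, did not know what was being tested. Here they do. The understanding outcome is subjective, is rated by users of the device, is tested in one direction and has no planned comparison between arms, so expectation alone could produce a favourable change. Caregivers' classification of situations, which feeds the primary analysis, is also unmasked.

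The mask that is described hides the arm. Most planned tests compare situations or time points within a patient, where hiding the arm changes nothing. For the before-after biomarker tests, the relevant mask for anyone making judgements on samples or ECG traces is the time point, and the Blinding section does not mention it. If the label stands, results from unmasked comparisons could be reported and read as coming from a blinded trial.

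**Working it through.** No figure in the protocol bears on this point, so the check sets the planned comparisons beside the stated mask.

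**Who knows what**
- *Alarms:* known to caregivers. The alarm is sent to them (HR monitoring of acute pain), and the Intervention section says that they are not blinded to it.
- *Arm:* not stated in words. Staff are trained in the new written routine and carry it out from a fixed week, and they sign compliance with the intervention protocol before each shift (Measures of treatment compliance). They can hardly fail to know when the change begins. This is a strong inference.
- *Aim:* known. The end-of-study items ask about satisfaction with heart rate as a means of communication (Table 3).

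**What the mask does for each comparison**

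| Planned comparison | Contrast | Does hiding the arm at analysis help? |
|---|---|---|
| Primary: heart-rate spike counts, suitable versus unsuitable situations | Within patient | No: there is no arm contrast, and the mask is limited to the secondary outcome |
| HRV and cytokines, before versus after | Within patient, over time | No: the contrast is between time points |
| HRV and cytokines, early versus delayed | Between randomised arms | Yes, for the analyst's choices |
| Caregiver understanding, start versus end | Within caregiver, over time | No: there is no arm contrast and the rater is unmasked |

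The mask fits one of the four kinds of comparison. The before-after biomarker row holds 1 (HRV) + 5 (cytokines) = 6 tests, none of which gains from it.

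**Can the mask be kept while the paired test is run?** Table 1 places cytokine and HRV collection in weeks 1, 4 and 6. The middle collection falls after two weeks of intervention in the early group, while the delayed group has not yet started. There are two readings of before and after:
1. *Baseline versus end of study (weeks 1 and 6 for everyone).* The arm is not needed to choose the samples, so the mask survives. It also does nothing for this test.
2. *Aligned to each group's own start.* The week 4 sample counts as after in the early group and before in the delayed group. Choosing the pair then needs the arm, or a coded label supplied by someone other than the analyst.

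The text does not say which reading is meant. On the second, the order of analysis matters: the early-versus-delayed comparison should be finished before start weeks are released.

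**The case against.** The strongest reply is that the protocol is open about most of this. The Intervention section says that caregivers are not blinded, the Discussion accepts that context reported through caregivers may be biased, and alerting caregivers is the tool under test, so they could not be masked to it. The word blinded appears only in the Discussion. All of that stands, and it makes the fault one of labelling more than of concealment. It does not make the label correct.

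Four stronger readings are tempting, and the protocol does not support them.
- *The blind protects nothing that matters.* The early-versus-delayed biomarker comparison is the only randomised contrast, and the plan ties it to the effect of the formal change. Hiding the arm from the analyst is a sensible mask for it.
- *Laboratory and ECG staff know which sample is the later one.* The protocol does not say so. Specimens carry a coded number and initials only (Administrative, ethical, regulatory considerations), and only de-identified data go to the project team. What can be said is that the stated mask does not extend to time point.
- *The paired test breaks the mask.* This follows only if samples are aligned to each group's start and no independently held code is used.
- *The primary outcome rests wholly on unmasked caregivers.* Heart-rate rises are detected by a program with a 2 SD rule and recorded automatically, and the target situation must meet numerical criteria (at least 10 episodes, at least 80% reproducibility). Caregivers supply the context, not the signal. Nothing shows that knowing the arm would bias this within-patient test.

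**Conclusion.** The point holds as a correction of a stated property. The trial is open-label for caregivers, and its one described mask protects one of four kinds of comparison, at the analysis stage only. The primary test, the six before-after biomarker tests and the understanding test are outside its reach.

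The most exposed result is caregiver understanding: subjective, one-tailed, rated by unmasked users of the device and without a between-arm comparison. The risk to instrument-based cytokine values is smaller. No size of bias can be derived from the protocol, and none is claimed.

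The conclusion rests on the Blinding section being a complete account of the masking, and on the inference that staff who are trained in and apply a new routine know when it started. The mismatch between the label and the Blinding section needs only the first of these.

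**What to change.** 1. **Discussion, opening and conclusion.** Replace the word blinded with: *open-label, with the analysis of the early-versus-delayed biomarker comparison masked to arm*. State there that situational context and perceived understanding are unmasked caregiver reports.
2. **Blinding section.** Name the outcomes that the mask covers. Extend it by coding blood, saliva and ECG records so that both arm and time point are hidden from those doing the assays and ECG processing until the values are locked. Someone who does not read the samples or traces should hold the codes.
3. **Order of analysis.** Run the early-versus-delayed comparison on dummy arm codes first. Release each patient's start week only afterwards, for any before-after test that needs it.

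The cost is a less favourable design label and a small amount of coding work. It needs no extra patients and no change in care. Step 2 cannot mask the caregiver ratings; for those, plain disclosure is the remedy.

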### Data collection

#### Clinical assessments

Demographic information (date of birth, gender) will be recorded at inclusion. Relevant medical history, including history of current disease, and information regarding comorbid diagnosis and known aetiology will be recorded at inclusion through conversation with legal representative and primary caregiver, as well as through medical records.

#### Caregivers’ reports of observed pain

Observable pain is measured using the Non-communicating Children's Pain Checklist (NCPC) for children, and Non-Communicating Adult Pain Checklist (NCAPC) for adults. NCPC is shown to be internally consistent, consistent over time, significantly related to pain intensity, sensitive to pain, and specific to pain [66]. NCAPC has shown equal reliability in assessing chronic pain in adult individuals with ID [67, 68]. Both have proved useful within pain research on participants with ID [67, 69]. Score on NCPC/NCAPC will be recorded at start of trial as this gives each participant a baseline score on how much pain is visible to caregivers prior to use of HR-monitoring.

#### HR monitoring of acute pain

Polar OH1 or Verity Sense armbands are used to calculate measures of HR [70–73]. The armband detects pulse at the upper arm (brachial artery), which is transmitted to a Microsoft Surface Pro research laptop (Fig. 4).

**Fig. 4 Fig4:**
[figure not shown]
Diagram of pipeline. The workflow starts with “HR-band monitoring” registering data, then processing, alerting caregivers, and gathering sensor and situational data for analysis. The final step is the interpretation and eventual publication of results. Abbreviations, HR: heart rate. Icons from flaticon.com

The laptop has a program that calculates whether the HR has risen substantially. This is done by calculating the average HR for the last 20 min. The program then calculates a measure for the variation of the HR within 20 min. If the HR increases by more than 2 standard deviations above the average HR, it sends a signal to alert the caregiver.

#### Contextual data collection

The research laptop has a registration page for providing contextual data. When an HR increase is detected, the page will automatically appear and ask for information to be provided.

The caregiver will be given four main categories: physiotherapy/stretching, putting on/taking off cast, personal lift use, and hygiene; in addition to “other” with a free text description (Fig. 5). The caregiver checks off stressors according to a pre-made selection of psychological triggers (e.g., excessive stretching, pinched skin, and hot water). Finally, the caregivers check off what signs of pain the patient did show. On all levels there is the possibility of selecting “other” to write in free text.

**Fig. 5 Fig5:**
[figure not shown]
Context data collection. Presumed triggers for the increased HR is categorized and reported in the computer program during the pre-intervention phase. The caregivers will always have the possibility of reporting freely under “other”. Icons from flaticons.com

#### HRV monitoring of prolonged pain

HRV is a non-invasive measure of parasympathetic nervous system activity [74, 75]. Lower levels of HRV (i.e., reduced parasympathetic nervous system activity) have been associated with both poor somatic and psychiatric health [76, 77]. Like the HR, HRV is calculated continuously through the Polar OH1 armband. Additionally, HRV will be assessed at rest with a portable electrocardiogram (ECG). The ECG will be collected at baseline, after two weeks of intervention in the early group, and at the end of the study period.

#### Biochemical measurements

We will collect blood and saliva samples to measure biomarkers for long-term pain and stress at baseline, after two weeks of intervention in the early group, and at the end of the study period.

Determinations for assessment of systemic evidence of inflammation include CRP and ferritin [78], as well as Nam [79, 80]. CRP and Nam will be analysed using marker-specific salivary kits. Blood samples will be analysed at Oslo University Hospital for haemoglobin, haematocrit, red blood cell count, white blood cell count, white blood cell differential, platelet count, erythrocyte sedimentation rate, CRP and ferritin.

Pain-related inflammatory biomarkers include MCP-1, IL-1RA, IL-8, TGFβ1, and IL-17 [81–88]. Analyses will be performed at the Department of Clinical Chemistry, Oslo University Hospital, Oslo, Norway, on an Integra 800 instrument following standard protocol Roche Diagnostics, IN, USA; for details of the diagnostics pipeline, please see [name] et al., 2022 [89].

PhD [name] will perform all analysis of inflammatory markers at Oslo University Hospital.

